**Ethical Considerations**

Participation in the study is entirely voluntary. All caregivers (parent or legal guardian) of the participants will be provided with written informed consent. The Informed Consent Form will be signed and dated by the caregiver before they enter the study or undergo the any intervention related to the study. The Investigator or their nominee will explain the details of the trial and provide a Participant Information Sheet, ensuring that the caregiver has had sufficient time to consider their infant participating or not. The Investigator will answer any questions that the caregiver has concerning study participation. The investigator or their nominee shall emphasise to them that consent regarding study participation may be withdrawn at any time without penalty or affecting the quality or quantity of their future medical care, or loss of benefits to which the participant is otherwise entitled.

One copy of the consent will be kept by the caregiver, and one will be kept by the Investigator. The trial will not be initiated before the protocol, informed consent forms and participant information sheets have received approval / favourable opinion from the NZ Health and Disability Ethics Committee (HDEC).

The process for obtaining participant informed consent will be in accordance with the REC guidance, and Good Clinical Practice (GCP) and any other regulatory requirements that might be introduced. The investigator or their nominee and the participant or other legally authorised representative shall both manually sign and date the Informed Consent Form before the person can participate in the study.

The decision regarding participation in the study is entirely voluntary. The investigator or their nominee shall emphasize to them that consent regarding study participation may be withdrawn at any time without penalty or affecting the quality or quantity of their future medical care, or loss of benefits to which the participant is otherwise entitled. No study specific intervention will be done before informed consent has been obtained.

If the Informed Consent Form is amended during the study, the investigator shall follow all applicable regulatory requirements pertaining to approval of the amended Informed Consent Form by HDEC and use of the amended form (including for ongoing participants).

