**Study Intervention**

Approximately 40 infants aged 2 to 3 months will be recruited for a 6-month study with the intervention starting at around 6 months of age – The NZ Ministry of Health and World Health Organisation recommended age for introducing complementary foods (ref).

The study will be conducted in two stages to enable completion within the tight timeframe. Thirty (30) of the recruited infants will be receive a dietary intervention based on a prebiotic food (candidate food) and 10 infants will receive a probiotic control known to show relevant immune benefit(s) and accepted as an ingredient in infant nutrition. These 10 infants will serve as a positive control to ensure that our study design and methods in principle can detect probiotic-related immune benefit. Envisaged probiotic controls are: *Bifidobacterium longum subspecies infantis (B. infantis)* (ref) and *Bifidobacterium animalis lactis (B. lactis)* (ref).

Researchers will supply the dietary intervention at no cost to the participant. The food will be given to the infants daily in appropriate amounts according to their age and stage of weaning. The amount of food given to the infant will not displace other foods of important nutrient composition in the infant’s diet. The infant will be introduced to the food with their first complementary foods and the food will be consumed daily for the 6-month period of the intervention.

Parents and guardians will be requested to have their infant consume the supplied candidate food or probiotic control each day for a total of 6 months (i.e. from when the child turns 6 months old until they turn 1 year of age). Adherence will be measured using information from a monthly questionnaire with parents or guardians on the average amount of candidate food consumed per day in the previous month.

Outcomes

Parents/guardians will complete daily records of illness through reporting the incidence, severity, and duration of the 9 signs of upper and lower respiratory tract and GI infections. This will be completed throughout the course of the study. Specific consent will be obtained to access medical records for infection-related GP visits, medication prescription and use, and hospitalisation events from 6 to 12 months of age. The infectious nature of the illness will be established by microbiological data, and/or the use of validated questionnaires.

Data Collection

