Data collection will be conducted in a clinical setting for baseline, when the child is 4-6 months (CF1), 9 months of age (CF3), and 12 months of age (CF6). Additionally, brief monthly questionnaires administered over the telephone or as a face-to-face interview will collect information on the dietary intervention adherence and recent health history.

**Questionnaires** (baseline, CF1, CF3, CF6)

From 4 to 6 months, brief monthly questionnaires will determine breastfeeding, formula feeding, and whether/what solids have been introduced. Brief exit interviews will determine participant burden and suggestions to improve engagement with the intervention.

**Anthropometry** (baseline, CF1, CF3, CF6):

Standardised anthropometric measurements will include weight and length. Measurements will be performed using calibrated age-appropriate instruments, including electronic scales and measurement mat with the children wearing light or no clothing. Measurement accuracy will be monitored by two parameters, the degree of refinement (recorded to 0.5 cm or 0.1 kg) and the degree of tolerance (measurement agreement between 1 cm and 0.1 kg). Three serial measurements from each infant will be calculated. Prior to the measurement of weight, infants will be required to have a nappy change if soiled.

**Diet** (CF1, CF3, CF6):

Adherence to the food targets will be determined by daily retrospective questionnaires, product counts, and photographs of food offered and waste. Dietary intake will be measured at CF1, CF3, and CF6 using 3-day weighed food records. Breast milk remains an important component of the diet during the age period in question, and has important impacts on both the GI microbiota and immune function. Breast milk volume will be measured. Infant formula can be captured directly by the diet record.

**Blood** (CF1 and completion):

Specific consent will be sought to collect two blood samples (CF1 and CF6). The blood sample will be collected by a trained phlebotomist and will be used to assess the following:

- The protective antibody response in plasma following the oral rotavirus which is administered in the standard immunisation schedule at 6 week, 3 months, and 5 months of age. (Isolauri 1995)
- The protective antibody response in plasma following the intramuscular pneumococcal vaccination which is administered at 6 weeks, 3 months, 5 months, and 15 months of age. (Bunout 2004, Perez, 2010)

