This feasibility study will determine the power for a subsequent RCT there no sample size calculations are required. The proposed sample size of 30 infants who will receive the feeding intervention and 10 infants will receive the active control (probiotic) for a period of 6 months. This sample target is based on an achievable recruitment rate of participants within a 12 month time frame and allows for follow up for 6 months.

In addition to classical case/control analyses, every infant will not only be sampled but also analysed before and after the prebiotic feeding, i.e. being assessed as a case/control pair, in addition to classical data analysis. This “personal” case/control pairwise analysis will account for differences in infant feeding before the actual intervention (e.g. duration of breast feeding, infant formula differences) and can be interpreted as a multiplexed n-of-1 trial.

The feasibility aspect of this study will assess compliance and rate of loss to follow up. This data will be used to inform a subsequent RCT. In previous studies and prevalence studies that we have conducted in 12 to 24 month old children the recruitment rate has been approximately 2 participants per week.

Statistical methods

A multiplexed n-of-1 clinical design trial design in which every infant is sampled before and after the intervention, and followed up. Thereby constituting its own case-control pair.

Data Management

Each participant will be assigned a trial identity code which will be allocated at enrolment to allow for link-anonymisation of data. The documents and database will also use infant date of birth. All personal data will be stored on an encrypted drive with links to personal information only being available to the study co-ordination team. Paper forms and hard copies will be stored in locked filing cabinets in secure sites. Data will be consolidated by each site using the REDCap (Research Electronic Data Capture) software (RW.ERROR - Unable to find reference:1572). This is a secure web application which is password protected and not accessible by third parties. REDCap will be managed at the University of Auckland. The investigator will also keep a screening log with details of all participants screened for the trial with their name, date of birth, NHI number, and trial number. The investigators will permit monitoring, audits, review, and regulatory inspections, providing direct access to source data/documents (where appropriate).

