All measures and entered data are double-checked against source documents. Trained personnel will conduct the study according to standard operating procedures and protocols. All incidents or deviations from the protocol will be documented. A major violation is defined as one that may impact subject safety, affect integrity of the study data and/or subject’s willingness to participate in the study. This is a serious discrepancy resulting from error, fraud or misconduct e.g. failure to obtain informed consent or a breach in randomisation procedures. Should a major violation occur HDEC will be notified. Adverse events will be reviewed by an internal clinician; should any events be deemed as concerning for the health of the child they will make a decision as to whether the child’s GP needs notification (if consented to do so) or in more extreme cases, will withdraw the child from the study and make recommendations for clinical care. Should caregivers (parent or legal guardians) not wish to provide GP details, the clinician will contact them directly in situations deemed necessary in his medical opinion. All essential documents, including source documents will be retained for a minimum period of 10 years following the end of the study.

Data Analysis

Integrated analysis of the multi-omics data from multiple platforms will be performed to visualise and interpret changes according to biological pathways and networks. This will be performed using software tools such as Ingenuity Pathway Analysis (IPA), mixOmics [Le Cao 2009], and metaCyc [Caspi 2014]. In additional to classical case/control analyses, every infant will not only be sampled but also analysed before and after the “prebiotic” feeding, i.e. being assessed as a case/control pair, in addition to classical data analysis. This “personal” case/control pairwise analysis will account for differences in infant feeding before the actual intervention (e.g. duration of breast feeding, infant formula differences) and can be interpreted as a multiplexed n-of-1 trial [24].

Clinical Pilot Study Objectives and Milestones

1. To determine whether infants will consume the target food(s) in a dose estimated to be sufficient to impact protection against infection *via* modification of the microbiome and associated metabolite changes.
2. Milestone 1: Amount of the candidate food(s) free-living infants are offered and consumed over the complementary feeding period (6 to 12 months of age).

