3. Milestone 2: Best method(s) to collect data on adherence to consuming the candidate foods (number attempted, number completed, quality).
4. To determine the feasibility of the outcome measurements (infection, immune, microbiome, host/microbe metabolome), assess recruitment potential, and identify high prevalence adverse events.
5. Milestone 1: Feasibility of measuring protection against infection using daily parental report of infection (number attempted, number completed, quality).
6. Milestone 2: Feasibility of measuring immune response to the rotavirus and pneumococcal vaccines in venepuncture blood and saliva as measures of immune function (% of children who followed the immunisation schedule, % of parents who agree to blood test, % successful blood draws in young children, data fit to purpose).
7. Milestone 3: Feasibility of using medical records as a measure of immune response
   (% of parents who agree to data access, completeness of data access, data fit to purpose).
8. Milestone 4: Feasibility and logistics of collecting 4 faecal samples between 6 and 12 months of age (number collected).
9. Milestone 5: Recruitment rate per month and extent and type of advertising required.
10. Milestone 6: Prevalence and nature of parent-reported adverse events, and identification of gross changes in growth rate.
11. To determine an appropriate sample size for the proposed full clinical trial.
    1. Milestone 1: Sample size required for the primary objective of the proposed clinical trial – improved immune protection from infection as a result of consuming the candidate food(s).
    2. Milestone 2: Sample size required for the secondary objective of the proposed clinical trial – altered microbiota as a result of consuming the candidate food(s).

Research Plan (2019 – 2024)

The present proposal aims at delivering the scientific insight and development concept to enable design and execution of a follow-up full clinical trial, informed by the pilot trial described in the present submission. The full-scale clinical study will test whether and how immune protection benefits can be conferred to infants around the weaning period by “targeted prebiotic feeding”. In contrast to the pilot trial (conducted at the Liggins Clinical Research Unit) this full trial is envisaged to be set up and performed at the “Starship Children's Health” Hospital, Auckland.

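### For the more extreme adverse events the protocol's stated action is to withdraw the infant from the study; it states no product-only stop and no follow-up afterwards, so later growth, illness and outcome data would ordinarily not be collected

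*Protocol*

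**What the plan says.** The only text on managing adverse events stands under Data Management. An internal clinician reviews events. For those of concern the clinician decides whether to notify the GP, where consent allows, or "in more extreme cases, will withdraw the child from the study and make recommendations for clinical care". Where caregivers give no GP details, the clinician contacts them directly if that is judged medically necessary.

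The only other exit described is the caregiver's: under Ethical Considerations, "consent regarding study participation may be withdrawn at any time without penalty".

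The data that depend on staying in the study are these:

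- **Growth.** "Standardised anthropometric measurements will include weight and length", taken at baseline, CF1, CF3 and CF6 (Anthropometry; Table 1). Feeding begins at CF1 (key to Figure 1).
- **Illness.** Parents keep daily records for the duration of the study (Outcomes).
- **Monthly contact.** Brief questionnaires "will collect information on the dietary intervention adherence and recent health history" (Data Collection).
- **Medical records.** "Specific consent will be obtained to access medical records for infection-related GP visits", and also for medication and hospitalisation, from 6 to 12 months of age (Outcomes).

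Under Clinical Pilot Study Objectives and Milestones, Milestone 6 of the feasibility objective reads: "Prevalence and nature of parent-reported adverse events, and identification of gross changes in growth rate".

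**The concern.** The rule makes the study, not the product, the thing that is stopped. Stopping exposure is the obvious clinical response to a serious event; ending observation is a separate decision, and the text joins the two. Followed as written, study observation ends for the infants with the worst events, and does so because of those events.

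Milestone 6 wants the nature of adverse events and any gross change in growth. For a withdrawn infant the study would record that the event happened, but would usually not learn whether it resolved or whether growth faltered afterwards. That information bears on whether the product is acceptable for the later RCT.

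**Working it through.** The protocol gives no figure to reproduce here: no expected adverse event rate, no withdrawal rate and no assumed loss to follow-up. The main check is therefore of the text, followed by arithmetic for scale.

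**Text check.**

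1. Action for more extreme events: withdrawal from the study plus care recommendations (Data Management).
2. Product-only discontinuation: not stated anywhere in the protocol.
3. Follow-up after a clinician withdrawal (event outcome, growth, illness record): not provided for anywhere, and not forbidden.
4. Growth after feeding starts: CF3 and CF6 only. An infant withdrawn before CF3 has no study growth measurement after feeding starts; one withdrawn between CF3 and CF6 has one of two.
5. Medical-record access: not said to lapse on withdrawal. As described it covers infection-related GP visits, medication and hospitalisation, so it would supply neither study growth measurements nor the daily record.

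**Scale.** Inputs from the protocol: 30 + 10 = 40 infants; two growth visits after feeding starts; a 6-month intervention. The withdrawal rates r below are assumptions.

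Expected withdrawals = 40 × r. Chance of at least one = 1 − (1 − r)^40.

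| Assumed r | Expected infants | Chance of at least one |
|---|---|---|
| 1% | 0.4 | 33% |
| 2% | 0.8 | 55% |
| 5% | 2.0 | 87% |

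Growth visits after feeding starts: 40 × 2 = 80. With k infants withdrawn before CF3, 2k are lost: k = 1 gives 2/80 = 2.5%; k = 2 gives 4/80 = 5.0%.

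Illness record, with withdrawal assumed one month into feeding: 5k infant-months are lost. The denominator is open.

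- Intervention months only, 40 × 6 = 240: 5/240 = 2.1% (k = 1), 10/240 = 4.2% (k = 2).
- From enrolment at 2 to 3 months up to 12 months, 40 × 9 = 360 to 40 × 10 = 400: 1.3% to 1.4% (k = 1), 2.5% to 2.8% (k = 2).

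By group, one withdrawal is 1/10 = 10% of the probiotic infants or 1/30 = 3.3% of the candidate-food infants.

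**Worst case for the growth milestone (assumed).** Suppose every withdrawn infant would have shown a gross growth change and a proportion p of the others do. The complete-data prevalence is p + (k/40)(1 − p), against p among those still observed, so the shift is (k/40)(1 − p).

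| p | k = 1 | k = 2 |
|---|---|---|
| 10% | 2.25 points | 4.5 points |
| 20% | 2.0 points | 4.0 points |
| 30% | 1.75 points | 3.5 points |

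For comparison, the exact (Clopper-Pearson) 95% interval for 8/40 = 20% is 9.1% to 35.6%. The worst-case shift is small against that sampling error. If withdrawn infants do not differ from the others there is no shift, only lost information.

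**The case against.** The strongest reply is that much of this rests on silence. The protocol does not forbid follow-up after withdrawal. Care recommendations and discretionary clinician contact remain, so the child is not abandoned. Parents are only requested to give the food daily, and nothing makes consumption a condition of staying in, so a family could stop the food, report no intake and still attend CF3 and CF6. Conduct is also referred to operating procedures that are not shown. Further, the governing objective is to identify high-prevalence adverse events, which rare extreme ones are not; the products are chosen as low-risk; every rate used above is assumed; and ending the study burden for a seriously ill infant is a defensible, cautious choice.

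Most of this stands as a limit on the point. A reader might infer that follow-up is prohibited, or that stopping the product alone is impossible. The text supports neither; it supports only that neither is provided for once the clinician acts on a more extreme event. What does not fall away is that the action written down for those events is withdrawal from the study. The remaining contact is clinical, not data collection. Milestone 6 also names the nature of events and growth changes, not prevalence alone.

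A reader might also infer a conflict with the Sample Size section, where "The feasibility aspect of this study will assess compliance and rate of loss to follow up". There is none: withdrawals can be counted under the present rule. Nor do the documents suggest that such events would be caused by the product.

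**Conclusion.** The point holds as a minor safety-follow-up weakness. For the infants with the worst events, the protocol as written would ordinarily leave growth at the remaining visits, the later daily illness record and the outcome of the event uncollected. Its size is unknown, since it depends on an event rate that the protocol does not give and on the clinician's undefined threshold for an extreme case.

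A reader might infer that the adverse event prevalence or group growth results would be seriously biased. The documents do not support that. The triggering event and all earlier data are kept, and even the assumed worst case for one or two infants moves growth prevalence by 1.75 to 4.5 points. The stake is what is learned about individual infants.

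**What to change.** In the adverse event text under Data Management, make discontinuation of the study product the clinician's action in place of withdrawal from the study. Then state the following.

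- With caregiver agreement, and unless the clinician judges continued participation unsafe, the monthly call, the daily illness record, CF3 and CF6 weight and length, and consented medical-record access continue. The event is followed to its outcome.
- The clinician keeps the authority to end participation for safety.
- Product discontinuation (date, reason) is recorded separately from study withdrawal and from loss to follow-up.
- Data after discontinuation are flagged as off-product. The plan is that "every infant will not only be sampled but also analysed before and after the prebiotic feeding", and off-product samples should not serve as the after-feeding half of that pair. Their use is for safety.

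The cost is a wording change in the protocol and information sheet, plus a discontinuation entry in the database. Apart from following the event to its outcome, the contacts are already planned. Some caregivers will decline and some extreme cases will still need full withdrawal, so part of these data will remain missing.

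### Blood and stool feasibility is scored by draws and samples, which does not show how many infants can enter the planned before/after pair analysis

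*Protocol*

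**What the plan says.** Under Statistical methods, the protocol describes a multiplexed n-of-1 design in which "every infant is sampled before and after the intervention, and followed up. Thereby constituting its own case-control pair". The Background, Sample Size and Data Analysis sections say the same. Sample Size and Data Analysis add that classical analyses will be run as well.

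Blood is optional and is taken twice. The Blood paragraph of Data Collection states: "Specific consent will be sought to collect two blood samples (CF1 and CF6". Table 1 marks it as opt in/out. Stool is planned at four ages in the Stools paragraph (6, 7.5, 9 and 12 months), and at Baseline, CF1, CF3 and CF6 in Table 1.

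Clinical Pilot Study Objectives and Milestones then sets out how feasibility will be measured. Under the outcome-feasibility objective, Milestone 2 (immune response to vaccines) lists the percentage "of children who followed the immunisation schedule, % of parents who agree to blood test, % successful blood draws in young children", followed by an undefined item on whether the data are fit for use. Milestone 4 reads "Feasibility and logistics of collecting 4 faecal samples between 6 and 12 months of age (number collected". No milestone counts infants who have both a before and an after sample.

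**The concern.** Feasibility of the outcome measurements is one of the pilot's primary objectives, and the pilot is meant to inform the design and size of a full trial. The Research Plan carries the before/after analysis into that trial. What the planners need from the pilot, for a paired outcome, is the share of enrolled infants who end up with a usable pair. The milestones report consent, draws and samples instead. Two infants show the problem. If one has only the CF1 draw succeed and the other only the CF6 draw, draw success is 2 of 4, or 50%, and there is no pair to analyse. A favourable draw rate or sample count could therefore be read as evidence that the paired analysis is feasible when the paired data are sparser.

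**Working it through.** **The plan's own figures.** Sample Size states: "The proposed sample size of 30 infants who will receive the feeding intervention and 10 infants will receive the active control (probiotic". That is 30 + 10 = 40, and Figure 1 agrees with 5 groups × 8 = 40. There is no power calculation to reproduce: "This feasibility study will determine the power for a subsequent RCT there no sample size calculations are required". The protocol gives no expected consent rate, draw success or stool yield, so every rate below is an assumption chosen to show the range.

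**Blood.** Let c be the number of consenting infants, with one scored draw at each of two visits, so 2c draws. Let S be the number of successful draws and s = S/(2c).

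- Most pairs: successes fall two to an infant, giving S/2 pairs, a share of s.
- Fewest pairs: successes are spread over as many infants as possible, giving max(0, S − c) pairs, a share of max(0, 2s − 1).

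With all 40 infants consenting (80 draws):

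| Assumed success | Successful draws | Fewest pairs | Most pairs | Paired share |
|---|---|---|---|---|
| 90% | 72 | 72 − 40 = 32 | 72/2 = 36 | 80–90% |
| 80% | 64 | 64 − 40 = 24 | 64/2 = 32 | 60–80% |
| 70% | 56 | 56 − 40 = 16 | 56/2 = 28 | 40–70% |

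If the two draws were independent within an infant, the share would be s²: 81%, 64% and 49%. These lie inside the bounds, and independence is itself an assumption.

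Consent widens the gap when the base is all enrolled infants. With 32 of 40 consenting and 51 of 64 draws successful (about 80%), pairs lie between 51 − 32 = 19 and 25 (51/2 rounded down), which is 47.5% to 62.5% of 40.

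Reporting success by visit does not help. With rates a and b at the two visits, the paired share lies between max(0, a + b − 1) and the smaller of a and b. For 80% at each visit, that is still 60% to 80%.

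The lower bound takes both planned draws of each consenting infant as the denominator. If only attempted draws were counted, infants lost before CF6 would drop out of it and the paired share could be lower still. The upper bound would not change.

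**Stool.** Four samples from 40 infants make 160. The protocol does not define which two samples form the stool pair. For illustration, take the 6- and 12-month samples. If T are collected, 160 − T are missing. Infants with both then number at least max(0, 40 − (160 − T)) and at most 40, as long as no more than 80 are missing.

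- T = 144 (90%): 40 − 16 = 24 to 40 infants, or 60–100%.
- T = 128 (80%): 40 − 32 = 8 to 40 infants, or 20–100%.

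The yield may thus lie above or below the paired share. These are mathematical limits, not expected values.

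**The case against.** The milestones are short prompts without denominators. The blood item could be tabulated per child, and the stool item could mean how many of the four samples each infant supplied. A statistical analysis plan might settle this. The same list also ends with a usability item ("of parents who agree to blood test, % successful blood draws in young children, data fit to purpose"), and Sample Size says loss to follow-up will be assessed. This has some force: per draw and per sample is the literal reading, not one the protocol spells out. But a per-visit or any-draw reading does not give the paired share either, and neither the undefined usability item nor the loss to follow-up rate supplies it. The protocol did not leave the measures open; it listed them, and they do not match an analysis it also states.

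It is also fair that the pair analysis is not the only one. An infant with a CF6 sample alone could still enter a group comparison. And because samples are planned by infant and visit, the paired count could be tabulated later, so no information is lost.

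Three stronger readings are tempting and are not supported:

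- **Vaccination.** A reader might infer that the schedule score must be 0%, because the protocol describes the "intramuscular pneumococcal vaccination which is administered at 6 weeks, 3 months, 5 months, and 15 months of age" and follow-up ends at 12 months. But a 12-month-old who has had every dose due by then can naturally be said to have followed the schedule, and the rotavirus doses end at 5 months.
- **Size of the full trial.** A reader might infer that it would fall short of pairs by a calculable amount. No rule in the protocol inflates its size by draw success. The stated sample-size targets are protection from infection and altered microbiota; paired blood is named for neither.
- **Stool.** A reader might infer that a 75% yield (120 of 160) could leave no pairs. That needs all 40 missing samples to be first or last ones, exactly one per infant. Table 1 also lists stool at Baseline as well as CF1, so one missing early sample need not break a pair.

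**Conclusion.** The point holds in a limited form. Read literally, the blood and stool measures in Milestones 2 and 4 do not determine how many infants can enter the before/after analysis. For blood the discrepancy has a known direction: with one scored draw per visit, the per-draw figure equals the paired share or overstates it, by as much as 20 percentage points at an assumed 80% success (60% against 80%). For stool the count does not identify the paired share, and no single size can be attached. The consequence is confined to the paired immune and microbiome outcomes. This is a poorly chosen feasibility measure that can be corrected from infant-level data, so it is a moderate weakness. It is still worth correcting in the protocol, because feasibility of these measurements is a primary objective.

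**What to change.** Reword Milestones 2 and 4 so that the main feasibility figure, separately for blood and stool, is the number and percentage of all enrolled infants with a usable pre-feeding (or start-of-feeding) sample and a usable CF6 sample, with a 95% CI. State for each sample type which visit supplies the before sample; for blood this is CF1. Keep consent, per-draw success and sample counts as supporting figures, each with its denominator, so that the step at which pairs are lost can be seen. Where the full trial is sized for a paired outcome, base any missing-data allowance on the paired share.

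This needs no additional sample, visit or burden on families: only the wording of two milestones and a few lines of tabulation. The drawback is that the headline percentages may look less favourable.
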